### Outcomes

#### Primary Outcomes

The primary outcome measures (Table 1) will be the following:

Preference reported for the gestational outcome (for a healthy woman and neonate) the safety of which is determined on the basis of evidence: waiting for spontaneous onset of labor; waiting for the full 39 weeks; preference for vaginal childbirth; preference for cesarean delivery after labor; preference for elective cesarean delivery; or indifference.Differences between the responses in the elaboration of the birth plan, aligned with the information provided in the intervention, in accordance with the Ministry of Health guidelines.Knowledge of the COVID-19 pandemic’s impact in childbirth care and alternatives available.

**Table 1 table1:** Outcomes of interest and definitions.

Endpoints	Definitions
Engagement in the intervention	Proportion of invited women who finish the missions
Reduced interest in elective cesarean section	Reduction in the proportion of women who intend to schedule an elective cesarean section
Increased engagement in seeking protagonism or informed choice	Proportion of women who develop a birth plan
Knowledge of the safest, most effective options associated with a more positive experience	Safer, more effective choices associated with a more positive experience in the exit survey and the birth plan
Engagement or desire to elaborate and share the experience and concerns	Elaboration of a narrative of the experience, doubts, and expectations regarding childbirth
Knowledge of the options available during the COVID-19 pandemic	Responses compatible with the information offered

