### Birth Plan

The birth plan is a structured means of reflecting on the desired care for labor and birth, including an assessment of possibilities and uncertainties arising from the COVID-19 pandemic. It allows assessing the understanding of the intervention through questions on topics such as companionship, mobility, episiotomy, the Kristeller maneuver (fundal pressure), and augmentation with oxytocin. Upon completing the questionnaire (Multimedia Appendix 7), the participant sees her consolidated birth plan and is encouraged to take a screenshot to save this information.

Participants in both the intervention and control arms will be invited to elaborate a birth plan, and we will compare the differences in engagement and the responses.

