### Parameters for Calculating the Sample Size

The sample size was calculated in accordance with the following parameters:

Study population size: in total, 32,000 women of reproductive age registered through the app (data collected from July 2019 before the onset of the COVID-19 pandemic).Prevalence of the outcome of interest: a prevalence of 2.6% (Murcia, Spain) and 3% (São Paulo, Brazil) in the delivery rate of the birth plan to the obstetric care service.Estimated impact of the intervention: a previous study that aimed to verify the effectiveness of a crowdsourcing strategy in promoting testing for hepatitis among men who have sex with men in China achieved a rate of 72.1% for the visualization of the multimedia components of the intervention. An increase in the number of tests performed was reported among 17.4% of the participants and confirmed by sending pictorial evidence of the examination among 7.9% of the participants [48]. In this study, a 20% impact on the outcome of preference for the elective cesarean section was estimated.Margin of error and safety: considering that part of the parameters used during sampling was estimated from other studies and the possibility of loss to follow-up among a portion of the recruited women, a type I error (α) margin of 1% was adopted with a 99% confidence level, along with a safety margin for type II error (β) of 20%.

Thus, at least 9068 participants in each group will be required to demonstrate the effect of the educational intervention on the outcome measures of interest [49]. We expect to have 10,000 participants in each group. Expected recruiting numbers (approximate, depending on engagement) are detailed in Multimedia Appendix 9.

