### Data Analysis Plan

#### Statistical Analysis

CONSORT (consolidated standards of reporting trials) guidelines will be used in reporting the results. An intention-to-treat analysis will be performed to compare data from the study's entry and exit surveys. This approach promotes a pragmatic assessment of the potential benefits of the intervention, as it incorporates loss to follow-up in the analyzed data of the intervention group.

Sociodemographic characteristics will be analyzed using descriptive statistics; between-group comparisons will be performed using chi-square analysis or a 2-tailed *t* test. For all group comparisons, the results shall be expressed as an effect (or relative risk for binary outcomes), corresponding 2-sided 99% confidence intervals (α=1%; power=80%), and associated *P* values. Adjusted analyses using baseline variables shall be performed using regression analysis to determine the continuing influence of key baseline characteristics on the outcomes, including female app users in the public and private sectors, cesarean sections, and vaginal delivery. The analyses will be conducted using the R statistical analysis software (The R Foundation) [53].

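### Three unranked primary outcomes, each judged at 1%, put the trial-wise false-positive rate at up to about 3% if any one of them counts as success

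*Protocol article*

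**What the plan says.** The Primary Outcomes subsection opens with "The primary outcome measures (Table 1) will be the following" and gives three items:

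- A reported preference for the outcome of pregnancy, with options that include "waiting for spontaneous onset of labor; waiting for the full 39 weeks; preference for vaginal childbirth; preference for cesarean delivery after labor", followed by elective cesarean and indifference.
- "Differences between the responses in the elaboration of the birth plan, aligned with the information provided in the intervention", judged against national guidelines.
- Knowledge of the pandemic's effect on childbirth care and of the alternatives available.

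Table 1 has six rows: completion of the missions, interest in elective cesarean, development of a birth plan, knowledge of safer options, a written narrative, and COVID-19 knowledge. Neither the list nor the table ranks anything or labels anything secondary. The Birth Plan section says that the plan asks "questions on topics such as companionship, mobility, episiotomy" and further topics.

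The Statistical Analysis section says "For all group comparisons, the results shall be expressed as an effect (or relative risk for binary outcomes", and adds "corresponding 2-sided 99% confidence intervals (α=1%; power=80" percent, together with P values. The sample size section says "a type I error (α) margin of 1% was adopted with a 99% confidence level" and sets the power at 80%. It gives the reason for the strict level as parameters borrowed from other studies and possible loss to follow-up.

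**The concern.** A 1% level protects the trial's conclusion only if one comparison carries that conclusion, or if a rule says how several comparisons combine. Here three outcomes have equal standing, each is reported against 1%, and the reader cannot tell which one decides. The reason given for the 1% is not multiplicity, so the strict level cannot be read as a correction already made for having several primaries.

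Two further features blur the target. The list and Table 1 disagree on what the primary set contains. The first listed outcome also combines when birth should begin with how it should happen, so there is no single yes/no variable to which one relative risk could apply. At stake is whether a claim of success means what the stated 1% implies, and whether the deciding result is fixed before the data are seen.

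**Working it through.** **The plan's own figure.** The article states no trial-wise error rate; the figure tied to the 1% level is 9068 per group. Inputs from the sample size section are a 3% base rate (birth-plan delivery), a 20% effect (read here as relative, so 3% against 3.6%), two-sided 1%, 80% power and a population of 32,000.

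- Simple formula: (2.5758 + 0.8416)² × (0.03×0.97 + 0.036×0.964) / 0.006² = 11.679 × 0.063804 / 0.000036 ≈ 20,699 per group; 20,704 with pooled variance under the null.
- Finite-population correction on the total: 41,408 / (1 + 41,407/32,000) ≈ 18,051, or about 9,025 per group, 0.5% below 9068.

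The correction is inferred from the listed population size and is not stated. Without it, the stated alpha and power give 14,647 to 24,381 per group across base rates of 2.6% to 3%, either direction of effect, one- or two-sided testing, and with or without continuity correction. Below, 9068 is simply taken as giving 80% power at two-sided 1%.

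**The list against Table 1.**

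- Elective cesarean: an option within the first listed outcome, and a row of its own in the table.
- COVID-19 knowledge: in both.
- Birth-plan responses: a listed outcome, but in the table only as part of the row on safer choices, which also draws on the exit survey.
- Mission completion, development of a birth plan and narrative writing: in the table only.

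**Chance of at least one false positive**, with k tests each at 1% and all null hypotheses true:

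- Independent tests, 1 − 0.99^k: k = 3 gives 1 − 0.9703 = 2.97%; k = 6 gives 1 − 0.9415 = 5.85%.
- Upper bound under any dependence, k × 1%: 3% and 6%.
- Equal pairwise correlation, by simulation with 500,000 draws: for k = 3, 2.9% at correlation 0.3, 2.7% at 0.5 and 2.2% at 0.8; for k = 6, 5.4%, 4.8% and 3.3%.

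The correlations are assumptions; the article gives none.

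**Cost of dividing the 1% instead of ordering the tests.** Bonferroni over three gives 0.333% each, with critical value 2.9352.

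- Sample size: 9068 × ((2.9352 + 0.8416)/(2.5758 + 0.8416))² ≈ 11,075 per group.
- Power at 9068: Φ(3.4174 − 2.9352) ≈ 68.5%.
- Power at 10,000: Φ(3.4174 × √(10,000/9068) − 2.9352) ≈ 74.3%.

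**Does the planned size support elective cesarean intention as the deciding outcome?** The article gives no base rate for it. For a 20% relative reduction at two-sided 1% and 80% power, the need per group is 482 at an assumed base of 55%, 1,278 at 30% and 2,154 at 20%. It reaches 9068 at a base of about 5.5%, and at 3% it would be 17,045.

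**The case against.** The best counter-argument is that this is a condensed article, and that testing order, multiplicity procedure and birth-plan scoring normally belong in an analysis plan that is not shown. That is fair as far as missing detail goes, and none of that detail is held against the document. What remains is stated text: an unranked primary list, a table that does not agree with it, and one 1% rule for all comparisons.

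It can also be said that 3% is still below a conventional 5%, and that inflation arises only if any one positive result counts as success. Both are true. The article gives no success rule, so the 3% is conditional, but nothing in the text excludes that reading.

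Several stronger readings are tempting and are not supported:

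- A reader might infer six co-primary endpoints. The table is titled as outcomes of interest, not primary outcomes. Mission completion reads as a process measure, and narratives are assigned to thematic analysis in the Qualitative Analysis section.
- A reader might infer that every preference option and every birth-plan topic is tested separately, giving a much larger count. The article does not say so; it names chi-square analysis, which can cover a categorical item in one test, and the birth-plan topics are only examples.
- A reader might infer that respondents could tick several preferences. The answer format is in an appendix that is not shown. The mixture of timing and mode is visible in the text; how it was asked is not.
- A reader might infer that about 20,000 women make a chance finding inevitable. Sample size does not raise the type I error rate.

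**Conclusion.** The point holds within limits. Three outcomes of equal standing, each judged at two-sided 1%, give a trial-wise false-positive rate of at most about 3%, and 2.2% to 2.7% at correlations of 0.8 to 0.5. This rests on any one positive result counting as success, which the article neither states nor rules out. The figure of about 6% applies only if all six rows of Table 1 were confirmatory, and that is not established.

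Separately from the arithmetic, the primary set is stated inconsistently between the list and the table, and the first listed outcome does not define one binary endpoint. The larger practical issue is that the deciding result is not fixed in advance; the numerical inflation is modest.

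**What to change.** Before outcomes are compared by arm, amend the Outcomes and Statistical Analysis sections as follows:

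- Name one deciding outcome, tested between arms at two-sided 1%. The proportion intending an elective cesarean at the exit questionnaire is a natural candidate: it is in both the list and Table 1, and it is the only outcome with an assumed effect in the sample size section. State its assumed base rate, which the article does not give.
- If that test succeeds, test one birth-plan alignment measure and then COVID-19 knowledge, each at 1%, in fixed sequence.
- Report mode preference and timing preference as separate variables.
- Label the remaining Table 1 rows secondary or descriptive.

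This holds the trial-wise rate at 1% without dividing alpha, so multiplicity adds nothing to the sample size. The price is wording, plus the demotion of two outcomes from primary to key secondary.

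If all three are to stay primary, Holm's procedure at a total of 1% also works, with some loss of power. Its strictest step is the 0.333% of Bonferroni, so power for a given outcome could fall from 80% to as low as about 68.5% at 9068 per group, or to about 74.3% at 10,000.

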### Participant Timeline

As the entire study will be carried out through a smartphone app, the study duration is shorter than that of regular trials. The first questionnaire (eligibility criteria filter) will be accessible to app users for 14 days. Once the user completes the questionnaire and is considered eligible for the study, her participation will last approximately 12 days (Multimedia Appendix 9).

### Parameters for Calculating the Sample Size

The sample size was calculated in accordance with the following parameters:

Study population size: in total, 32,000 women of reproductive age registered through the app (data collected from July 2019 before the onset of the COVID-19 pandemic).Prevalence of the outcome of interest: a prevalence of 2.6% (Murcia, Spain) and 3% (São Paulo, Brazil) in the delivery rate of the birth plan to the obstetric care service.Estimated impact of the intervention: a previous study that aimed to verify the effectiveness of a crowdsourcing strategy in promoting testing for hepatitis among men who have sex with men in China achieved a rate of 72.1% for the visualization of the multimedia components of the intervention. An increase in the number of tests performed was reported among 17.4% of the participants and confirmed by sending pictorial evidence of the examination among 7.9% of the participants [48]. In this study, a 20% impact on the outcome of preference for the elective cesarean section was estimated.Margin of error and safety: considering that part of the parameters used during sampling was estimated from other studies and the possibility of loss to follow-up among a portion of the recruited women, a type I error (α) margin of 1% was adopted with a 99% confidence level, along with a safety margin for type II error (β) of 20%.

Thus, at least 9068 participants in each group will be required to demonstrate the effect of the educational intervention on the outcome measures of interest [49]. We expect to have 10,000 participants in each group. Expected recruiting numbers (approximate, depending on engagement) are detailed in Multimedia Appendix 9.

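### The 9068 per group does not validly follow from its listed inputs, so the stated 80% power is unsupported for any outcome the trial measures

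*Protocol article*

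**What the plan says.** All the inputs are in the Protocol article, Parameters for Calculating the Sample Size:

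- Population: "Study population size: in total, 32,000 women of reproductive age registered through the app", dated July 2019.
- Base rate: "a prevalence of 2.6% (Murcia, Spain) and 3% (São Paulo, Brazil) in the delivery rate of the birth plan to the obstetric care service". The section presents this as the figure for its target outcome.
- Effect: "a 20% impact on the outcome of preference for the elective cesarean section was estimated".
- Error rates: "a type I error (α) margin of 1% was adopted with a 99% confidence level", and "a safety margin for type II error (β) of 20" per cent.
- Loss to follow-up is mentioned as a possibility, without a rate.

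The section concludes that "at least 9068 participants in each group will be required to demonstrate the effect of the educational intervention on the outcome measures of interest", and expects 10,000 per group. It names no formula. Statistical Analysis carries the error rates forward: "corresponding 2-sided 99% confidence intervals (α=1%; power=80" per cent). In Table 1 (Primary Outcomes) the cesarean endpoint is defined as "Reduction in the proportion of women who intend to schedule an elective cesarean section".

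**The concern.** A two-arm sample size for a binary outcome needs a base rate and an effect for the same outcome. Here no outcome has both. The base rate describes delivery of a birth plan to a care service. The primary outcomes cover reported preferences, birth-plan responses and COVID-19 knowledge, and Table 1 counts women who develop a plan. Nothing records handing it over. The effect belongs to elective cesarean preference, which has no base rate.

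Population size is also listed as a parameter. It matters when estimating a quantity in a fixed population, not when testing a difference between randomised arms.

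At stake is how the results are read. The 80% power claim is attached to the outcome measures in general and repeated in the analysis section. A null result would be read as coming from a trial with 80% power for a 20% effect, yet the document does not establish that for any measured outcome.

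**Working it through.** **Inputs.** Base rates 2.6% and 3%, a 20% change read as relative, alpha 1%, power 80% and N = 32,000 come from the sample-size section. Two-sided testing comes from Statistical Analysis, and 1:1 allocation from the Abstract. z(0.995) = 2.5758; z(0.80) = 0.8416.

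**Formula.** Two proportions, pooled variance under the null, with p̄ the mean of p1 and p2:

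n per group = [2.5758·√(2p̄(1−p̄)) + 0.8416·√(p1(1−p1) + p2(1−p2))]² / (p1−p2)²

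**Trying to reproduce 9068.** For 3% against 3.6%, p̄ = 0.033:

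- 2.5758 × 0.25263 = 0.65073, and 0.8416 × 0.25259 = 0.21259.
- n = (0.86332)² / 0.006² = 0.74532 / 0.000036 = 20,703 per group (21,035 with continuity correction).
- With a finite-population correction on the total: 41,406 / (1 + 41,405/32,000) = 18,050, or 9,025 per group.
- The same correction after continuity correction gives 9,088 per group.

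These two values lie either side of 9068, both within 0.5% of it; neither equals it. At the stated base rates and error rates, no variant without the finite-population correction (pooled, unpooled or arcsine, one- or two-sided) comes within 3%.

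**All four readings of the listed inputs** (20% relative change, two-sided alpha 1%):

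| Change | n per group for 80% power | With correction for 32,000 | Power at 9068 | Power at 10,000 |
|---|---|---|---|---|
| 3% to 3.6% | 20,703 | 9,025 | 37.7% | 42.0% |
| 3% to 2.4% | 17,044 | 8,253 | 46.7% | 51.7% |
| 2.6% to 3.12% | 23,997 | 9,600 | 31.7% | 35.6% |
| 2.6% to 2.08% | 19,739 | 8,837 | 39.8% | 44.3% |

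Power for the first row at 9068: (0.006·√9068 − 0.65073) / 0.25259 = (0.57136 − 0.65073) / 0.25259 = −0.314, and Φ(−0.314) = 37.7%.

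**Elective cesarean preference.** The document gives no base rate, so these control rates are assumptions. For a 20% relative reduction:

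| Assumed control rate | n per group for 80% power |
|---|---|
| 5% | 10,037 |
| 5.1% | 9,831 |
| 5.5% | 9,081 |
| 10% | 4,781 |
| 20% | 2,153 |
| 30% | 1,277 |
| 50% | 577 |

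So 9068 per group reaches 80% power from a control rate of about 5.5%, and 10,000 from about 5.1% (80.8% power; at exactly 5% it is 79.8%). If the 20% means absolute points, n is under 150 per group (for example 139 for 50% to 30%), further still from 9068.

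**The case against.** The strongest reply is that the low power belongs to an outcome the trial does not measure. For elective cesarean preference, the only outcome given an effect size, a control rate above 5.5% would make 9068 ample, and nothing in the document suggests a lower rate. This stands. A reader might infer from 32% to 47% that the trial is underpowered; the document does not support that, because those figures describe no planned comparison. Nor can one say that on the listed inputs the trial would always miss a 20% effect more often than find it: for 3% to 2.4% at 10,000 per group, power is 51.7%.

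A second reply is that 32,000 is a listed input and using it nearly recovers the figure. That also stands, which is why the point is that 9068 does not validly follow. But the reconstruction is only probable. It needs 3% rather than 2.6%, and a rise, whereas the cesarean endpoint is a reduction. Other near matches need inputs the plan does not state for this purpose: 3% against 3.75% at two-sided alpha 5% gives 9,100, and 6.58% against 7.9% at alpha 1% gives 9,050, where 7.9% is a test-confirmation rate from the cited hepatitis study.

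A reader might also infer that Study Setting has superseded the 32,000. It has not been shown to: the figures there (about 1,360,000 active users, 98,518 recently online) are not restricted to women of reproductive age.

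**Conclusion.** The concern holds in this form: the sample-size section combines a base rate for one outcome with an effect on another, and the resulting 9068 is roughly 38% to 53% of what those inputs require (9068/23,997 to 9068/17,044). This part rests only on the printed inputs, a relative reading of 20%, and a standard two-proportion test. That a finite-population correction produced the figure is a likely explanation, not an established one, and the conclusion does not depend on it. What is unsupported is the statement of 80% power, not the adequacy of the recruitment target. Actual power for elective cesarean preference cannot be computed from the document, and it could be well above 80%: at an assumed 10% control rate it is 98.3% with 9068 per group.

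**What to change.** Keep 10,000 per group and rewrite the calculation:

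- Remove the birth-plan delivery rate and the 32,000 population size.
- Name one measured outcome: intention to schedule an elective cesarean at exit, compared between arms.
- State that the 20% is relative, if that is what is meant.
- Restate the power, for example: two-sided alpha 1%; with 10,000 analysed per group, at least 80% power for a 20% relative reduction if control prevalence is 5.1% or more (about 5.5% or more with 9068 analysed).
- Take the base rate from entry-questionnaire responses pooled across arms and without arm labels. Use the pilot only if it recorded this item; the article describes it as a check of language and mission sequence.
- If an outcome with a 2.6% to 3% base rate is kept, give its power at 10,000 per group as 36% to 52%.

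The cost is rewording one section and one pooled tabulation, with no added participants. The downside is that the stated power becomes conditional on a base rate and on the number analysed, and may look less favourable.
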